### Data analysis

Outcomes of eligible patients who were randomly offered HBOT will be compared with eligible patients who were randomly selected from the control group. In case of non- or incomplete compliance with the intervention (i.e., patients not finishing all 30–40 HBO sessions), a worst-case analysis will be performed: dropped-out patients will be classified as non-responders. As part of the TwiCs design, non-compliance is only expected in the intervention group. In addition, patients in the control group may also undergo HBOT outside the trial setting. To account for the non-compliance in the intervention group and possible contamination in the control group, a Complier Average Causal Effect (CACE) analysis will be used in addition to the intention to treat analysis [21, 22]. In a CACE analysis, the group who accepted the HBOT will be compared to the control group who would have accepted the intervention if they had received the offer.

The primary outcome will be presented in absolute numbers and proportions. The primary outcome is defined as difference in proportion of patients with moderate/severe pain at 3 months follow-up per allocated treatment arm (i.e., intervention or control group). As pain is measured on a 4-point Likert scale, it will be dichotomized into no/mild pain and moderate/severe pain. Pain response is defined as decrease in pain from self-reported moderate/severe pain to no/mild pain. Differences in pain response will be compared by *χ*^2^ test. As secondary analysis, an unadjusted logistic regression analyses will be performed. In addition, as sensitivity analysis, the logistic regression analysis will be adjusted for age, time since radiotherapy, radiotherapy dose, and smoking. There will potentially be missing data. Assuming that missing values are missing at random, multiple imputation by chained equations for the primary analysis will be used to replace missing values, using 20 imputed datasets [23–26]. In addition, complete case analysis will be performed as sensitivity analysis. Toxicity will be presented as the overall incidence of grade 2–4 toxicity. QoL outcomes will be evaluated at 3 time points: baseline in the UMBRELLA cohort, prior to HBOT, and at follow-up. To account for the intra-subject correlation over time, a mixed model for repeated measurements will be used. In the model, a random intercept and random linear time effect and an autoregressive covariance structure of the first order (AR1) (assuming that the correlation systematically decreases with increasing distance between time points) will be included [27]. Also, fixed effects for treatment arm and an interaction between time and treatment arm will be included, as well as characteristics with imbalances as previously described. Differences with a *P* value < 0.05 will be considered statistically significant.

Given the relatively small sample size of the study, we will not be performing an interim analysis, as it is very unlikely that we will see a highly significant effect of HBOT justifying early stopping of the trial. Also, there is ample clinical evidence that HBOT is safe and associated with a very small risk of mild side effects. Therefore, no side effects are expected that might lead to early termination of the study. Consequently, no interim analysis was planned for this study.

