**Fig. 1 Fig1:**
[figure not shown]
Design of the UMBRELLA HONEY trial; a trial within cohorts design (TwiCs design), figure adapted from Relton et al. [10]

Patients with late radiation toxicity will be eligible for participation in the HONEY trial. In order to identify patients with late radiation toxicity, a self-developed late radiation toxicity questionnaire will be sent out to UMBRELLA participants who are > 12 months after the last radiotherapy fraction. The late radiation toxicity questionnaire consists of questions from different validated questionnaires. Breast and chest wall pain, social functioning, and other breast symptoms will be assessed with questions from the European Organisation for Research and Treatment of Cancer Quality of Life Questionnaire C30 (EORTC QLQ-C30), the breast-specific questionnaire EORTC QLQ-BR23, and Common Terminology Criteria for Adverse Events [13, 14]. In addition, specific questions were added by the researchers to assess possible late radiation toxicity in further detail and to evaluate eligibility criteria for the HONEY trial.

Eligibility criteria include self-reported breast pain or chest wall pain score in the late radiation toxicity questionnaire of 3 or 4 (on a scale of 1 to 4) and completed primary treatment for breast cancer (except endocrine treatment). Patients are ineligible when they were previously treated with HBOT, have contraindications for HBOT (e.g., (severe) COPD/asthma, pacemaker, morbid obesity, epilepsy in medical history, severe heart failure), and have current metastatic disease or recurrent breast cancer or when they are poor responders to UMBRELLA questionnaires (i.e., return of ≤ 2 questionnaires).

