### Randomization and informed consent

In addition to the primary endpoints, other effects for the patients receiving hyperbaric oxygen therapy (i.e., tissue oxygenation, side effects of HBOT, physician-reported outcomes) will be important to evaluate. As a large effect was assumed, the sample size needed to demonstrate a significant effect was rather small. Therefore, in order to be able to answer secondary research questions, a 2:1 ratio for HBOT vs. control group randomization was applied to increase the size of the intervention arm.

A computer-generated randomization list with varying block sizes (*n* = 3–6) will be generated by an independent data manager prior to the first inclusion. Randomization will be stratified for time since inclusion in the UMBRELLA cohort (i.e., ≤ 2.5 years or > 2.5 years after start radiotherapy). The randomization list is linked to a specially designed inclusion database in Microsoft Access. The investigator has no access to the randomization list. After enrolment in the inclusion database, Microsoft Access will allocate patients to their respective treatment.

In accordance with the TwiCs design, patients randomized to the HBOT arm will be contacted by the investigator and offered to undergo HBO treatment. If they agree, they sign a second informed consent form in addition to the previously signed informed consent form of the cohort. Also, patients have the option to consent for the use of their clinical data for other studies on the same subject. In case patients drop out after providing informed consent, patients are asked for permission for the use of their clinical data in the trial. This trial does not involve collecting biological specimens for storage. The informed consent form is available from the corresponding author upon request. Patients who refuse the offer to undergo HBOT will receive treatment as usual, i.e., standard follow-up. Standard follow-up may entail physiotherapy, edema therapy, and/or analgesics, depending on the patient’s needs. Patients who are allocated to the control arm will not be informed about the HONEY trial, and undergo standard follow-up. For logistic reasons and planning of HBOT, patients will be recruited in batches (Fig. 2). After confirmation of diagnosis by a radiation oncologist, patients provide informed consent and will be referred for hyperbaric oxygen therapy.

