### Primary and secondary endpoints

The primary endpoint of this study is the difference in proportion of patients with severe/moderate reported breast/chest wall pain between both groups at 3 months follow-up (Fig. 2). Upon inclusion, all patients will have moderate/severe pain, as this is an inclusion criterion. Self-reported pain is assessed through the late radiation toxicity questionnaire on a 4-point Likert scale (i.e., none/mild/moderate/severe). Self-reported pain is dichotomized into none/mild pain and moderate/severe pain.

Secondary endpoints include physical functioning, QoL, cosmetic outcome, physician-reported pain and radiation toxicity, tissue oxygenation, and side effects of HBOT. Physical functioning will be evaluated using the late radiation toxicity questionnaire, containing questionnaires on breast and arm edema, arm mobility, and breast fibrosis. QoL will be assessed by means of the EORTC QLQ-C30 and breast-specific questionnaire EORTC QLQ-BR23 [13]. In the UMBRELLA cohort, QoL is measured upon inclusion (before start radiotherapy), at 3 months, and every 6 months afterwards. Self-reported cosmetic outcome will be assessed using the BREAST-Q questionnaire [15, 16]. Depending on previous surgery, patients fill out a different module (mastectomy/breast conserving therapy/reconstruction) yearly within the UMBRELLA cohort. Side effects will be monitored using the MacFie classification [17].

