### Sample size considerations

Since moderate/severe pain is an inclusion criteria, all patients will have moderate or severe pain upon inclusion. We assume that 3 months after the last hyperbaric oxygen session, the proportion of patients treated with HBOT suffering from moderate to severe pain will decrease to 30% [5]. Both control patients and patients who refuse HBOT will receive usual care. It is not expected that the offer of HBOT will influence the outcome at follow-up. Consequently, we assume that of the patients receiving usual care, at least 80% will be reporting moderate/severe pain at the same time point.

It is expected that 50% of the women in the HBOT arm, who will be offered HBOT, will accept and undergo the treatment. As such, in the intervention arm, the overall proportion of women reporting moderate to severe pain will be 55% (0.5 × 30% + 0.5 × 80%) and 80% in the control group. In line with the TwiCs design, the control patients are not informed about the HBO treatment. Consequently, there will be no refusal in the control arm.

The purpose of this study is to evaluate if HBOT is either similar or better than usual care. Therefore, a directional (i.e., one-sided) test will be used. To demonstrate a significant difference of 55% vs. 80% with a power of 80%, a one-sided alpha of 0.05, and an inclusion ratio of HBOT vs. control group of 2:1, we need 72 patients in the HBOT arm and 36 patients in the control group. However, drop-out might be expected. These are not patients who refuse participation, but drop-out for other reasons, such as patients who no longer wish to participate in the UMBRELLA cohort or patients who accept the offer of HBOT, but drop-out afterwards. In order to adjust for 10% drop-out, a total of 120 (80:40) patients will be enrolled in the UMBRELLA HONEY trial. Enrollment is expected to take 20 months.

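### Baseline pain grade (3 or 4) enters no stated analysis of the primary endpoint, and the primary χ² test is not stratified as randomised

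*Protocol article*

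**What the plan says.** All references are to the protocol article; no separate SAP is at hand.

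- **Primary endpoint** (Primary and secondary endpoints): the "difference in proportion of patients with severe/moderate reported breast/chest wall pain between both groups at 3 months follow-up". Data analysis defines response as a move from moderate/severe to none/mild pain and compares it by χ² test, naming no stratum or covariate.
- **Other analyses of this endpoint** (Data analysis): "As secondary analysis, an unadjusted logistic regression analyses will be performed". Then, as a sensitivity analysis, "the logistic regression analysis will be adjusted for age, time since radiotherapy, radiotherapy dose, and smoking".
- **Randomisation** (Randomization and informed consent): "Randomization will be stratified for time since inclusion in the UMBRELLA cohort", with the cut at 2.5 years after the start of radiotherapy.
- **Baseline pain** (Study design): "Eligibility criteria include self-reported breast pain or chest wall pain score in the late radiation toxicity questionnaire of 3 or 4", on a 1–4 scale. The grade is therefore known for every patient before allocation.
- **Imbalance**: Data analysis provides for adjusting for imbalanced characteristics in the quality-of-life mixed model only.
- **Error rate** (Sample size considerations): "a one-sided alpha of 0.05", for 55% against 80% with 72 and 36 evaluable patients and 80% power.

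**The concern.** The endpoint counts anyone at grade 1 or 2 as a responder. A grade-3 patient needs to improve by one level and a grade-4 patient by two. The definition thus makes baseline grade a likely strong predictor, more directly than radiotherapy dose or smoking, which are in the adjusted model. Grade is not a randomisation factor either, so nothing in design or analysis controls it, and about 36 controls leave room for a visible imbalance.

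The Discussion itself describes a small randomised HBOT trial in head-and-neck cancer in which complaints before treatment differed between arms despite randomisation. If that happened here with pain grade, no stated analysis would show how much of the result was due to it.

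The stratum is a smaller matter. The usual practice is to analyse as randomised, and the primary test does not.

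**Working it through.** **1. The plan's own figure.** Inputs from Sample size considerations: control 0.80, HBOT arm 0.55, one-sided α 0.05, power 0.80, allocation 2:1.

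Controls needed = [z₀.₉₅·√(1.5·p̄(1−p̄)) + z₀.₈₀·√(0.80·0.20 + 0.55·0.45/2)]² / 0.25², with p̄ = (0.80 + 2×0.55)/3 = 0.633.

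= (1.645×0.590 + 0.842×0.533)² / 0.0625 ≈ 32.2, so 33 + 66 = 99. With continuity correction it is 38 + 76 = 114. The stated 72 + 36 = 108 lies between these. Exact power at 36 and 72 is 0.784 (Fisher or corrected χ²) and 0.845 (uncorrected χ²). The stated size is consistent with about 80% power, and 108/0.9 = 120 gives the enrolled number.

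**2. Chance imbalance in grade.** The article does not give the share f at grade 4, so it is assumed. SD of the between-arm difference = √[f(1−f)(1/36 + 1/72)] = √[f(1−f)×0.04167].

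- f = 0.2: √0.00667 = 8.2 points
- f = 0.3: √0.00875 = 9.4 points
- f = 0.4: √0.0100 = 10.0 points
- f = 0.5: √0.01042 = 10.2 points

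**3. Power of the stratified test.** Simulation of 200,000 trials per scenario with 36 against 72 patients, overall rates 80% and 55%, half the patients in each time stratum, no missing data, and the same conditional odds ratio (OR) of grade 4 against grade 3 for persisting pain in both arms. The OR is also an assumption. For scale, at f = 0.3, OR 2 means control persistence of about 77% and 87% (0.7×0.77 + 0.3×0.87 = 0.80). OR 5 means about 74% and 94% (0.7×0.742 + 0.3×0.935 = 0.80).

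One-sided power, time stratum not prognostic:

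| OR of grade | χ² | Mantel–Haenszel, grade × time, f = 0.2 / 0.3 / 0.4 | Change (points) |
|---|---|---|---|
| 1 | 0.844–0.846 | 0.838 / 0.834 / 0.835 | −1.0 to −0.8 |
| 2 | 0.845 | 0.841 / 0.842 / 0.844 | −0.4 to −0.1 |
| 3 | 0.844–0.845 | 0.847 / 0.850 / 0.854 | +0.3 to +0.9 |
| 5 | 0.844–0.845 | 0.856 / 0.862 / 0.870 | +1.2 to +2.5 |

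At OR 8, stratifying by grade alone gives 0.863–0.887 (+2 to +4.3). Stratifying by the time stratum alone changes power by −0.2 points (stratum OR 1) to +0.4 (stratum OR 2). Type I error of the stratified test is at or below 0.05.

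**4. What happens when an imbalance occurs.** Averages hide this. Take f = 0.30–0.45 and about 20 points more grade-4 patients in the HBOT arm, roughly 2 SD. Power of the χ² falls to 0.72–0.73 (OR 3) or 0.67–0.69 (OR 5), while the grade-stratified test stays at 0.85–0.87. With the reverse imbalance and no true effect, χ² rejects in 8–11% of such trials (OR 3–5) and the stratified test in about 5% or less.

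**The case against.** An unstratified χ² on a randomised comparison is valid. Averaged over all randomisations, its type I error already covers chance imbalance, and ignoring a stratification factor makes it conservative at most. That stands: the point concerns efficiency and robustness and identifies no error.

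A reader might infer that the plan gives away power or is underpowered. The article does not support this. It gives neither the grade 3/4 split nor any prognostic strength, and the gain is near nil up to OR 2. The χ² meets its target on the one-sided test that Sample size considerations specifies. Two-sided at 0.05 its power would be about 0.75, but whether the test is one-sided is a separate question.

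The stratum part is thin. Time since radiotherapy, essentially the variable behind the stratum, is in the sensitivity model, so the gap is confined to the primary and unadjusted analyses.

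Two further criticisms are tempting and do not hold. One is that a χ² cannot be used with the 20 imputed datasets: procedures for combining χ² statistics exist, and the difference in proportions pools directly. The other is that the unadjusted logistic regression is redundant: it supplies an odds ratio and is a harmless reference for the adjusted one.

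The objection does not remove the baseline-grade gap. The article itself fixes the test and lists the covariates, and baseline grade is in no stated analysis of this endpoint.

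**Conclusion.** The point holds as a recommendation to improve a valid primary analysis. Baseline pain grade should be used because the endpoint definition makes it a likely strong predictor and it is known before allocation. The expected change in average one-sided power is small: about −1 point if neither factor is prognostic, roughly nil at OR 2, up to +1 at OR 3 and +1 to +4 at OR 5–8. The stronger argument is protection against an imbalance with an SD of about 8–10 points. These figures rest on assumed values: 20–40% at grade 4 for power, 20–50% for the SD, a common OR in both arms, equal time strata and complete data. That grade is a strong predictor is inferred from the endpoint definition; the article gives no data on it.

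**What to change.** Before outcome data are examined:

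1. Make the primary analysis a Mantel–Haenszel risk difference and test, stratified by baseline pain grade (3 or 4) and the randomisation stratum as used for allocation. With 2:1 allocation the stratum weights are close to proportional to stratum size, so the result still describes a difference in proportions between arms.
2. Pool the risk difference and its standard error over the imputed datasets.
3. Add baseline grade to the adjusted logistic model.
4. Keep the plain χ² as a supporting analysis.
5. State which item supplies the grade if breast and chest wall pain are scored separately.

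No new data are needed, since grade comes from the eligibility questionnaire. The cost is about 1 point of power if neither factor is prognostic (about half a point when stratifying by grade alone), and sparse cells. Four strata share about 36 controls, on average 36/4 = 9 each, and with 20% at grade 4 only 36×0.2×0.5 = 3.6 in each grade-4 cell. A pre-stated rule to collapse to grade alone if a cell is empty in one arm would deal with that.

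### The named primary analysis, a chi-square test on 20 imputed datasets read at P < 0.05, does not by itself deliver the planned one-sided test or an interval for the declared difference in proportions

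*Protocol article*

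**What the plan says.** Four choices are stated in the protocol article.

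- **Sidedness** (Sample size considerations): "a directional (i.e., one-sided) test will be used". The calculation uses "a power of 80%, a one-sided alpha of 0.05, and an inclusion ratio of HBOT vs. control group of 2:1", for 55% against 80% with moderate or severe pain, and concludes "we need 72 patients in the HBOT arm and 36 patients in the control group". Allowing for 10% drop-out, 120 patients (80:40) are enrolled.
- **Primary quantity** (Data analysis): "The primary outcome is defined as difference in proportion of patients with moderate/severe pain at 3 months follow-up per allocated treatment arm". It is to be presented as counts and proportions.
- **Primary test and threshold** (Data analysis): pain response is compared by a chi-square test, and P < 0.05 counts as significant. The one-sidedness is not repeated.
- **Missing data** (Data analysis): "multiple imputation by chained equations for the primary analysis will be used to replace missing values, using 20 imputed datasets", under missing at random, with complete cases as a sensitivity analysis.

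For the secondary analysis, "an unadjusted logistic regression analyses will be performed". An adjusted version is a sensitivity analysis.

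**The concern.** Each choice is defensible alone, but together they do not produce the declared result. A chi-square statistic is the same kind of number whichever arm does better, so a threshold of P < 0.05 on it is a two-sided rule. Pooling chi-square statistics over imputed datasets again gives an unsigned statistic, with no pooled standard error for the difference in proportions. An analyst who follows the Data analysis section literally therefore runs a different test from the one that justified 108 evaluable patients, and has no interval for the primary quantity that reflects the missing data.

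At stake are about ten points of power at the planned effect, and a primary P value whose reading as one-sided or two-sided could decide the trial.

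**Working it through.** **Inputs.** From Sample size considerations: 80% control, 55% intervention, 2:1 allocation, one-sided 0.05, 36 and 72 evaluable, 40 and 80 enrolled. From Data analysis: 20 imputations. The missing fractions are assumptions (5% to 30%), since the article gives only the 10% drop-out allowance.

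**1. The plan's own figure.** The usual two-proportion formula (one-sided 0.05, 80% power, 2:1) gives 33/66 without continuity correction and 38/76 with it. A continuity-corrected version using the simple average proportion gives 36.75, so 37/74. Exact one-sided power at 36/72 is 0.784 for Fisher's test and 0.845 for the uncorrected chi-square. The stated 36/72 is thus close to a corrected one-sided calculation, and 108/0.9 = 120. The sample size is not in dispute here.

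**2. What sidedness alone does, with complete data.** Power = Φ[(0.25 − z·SE0)/SE1].
- Pooled proportion = (36×0.80 + 72×0.55)/108 = 0.6333.
- SE0 = √[0.6333×0.3667×(1/36 + 1/72)] = 0.0984.
- SE1 = √[0.16/36 + 0.2475/72] = 0.0888.
- One-sided, z = 1.645: Φ(0.99) = 0.84.
- Two-sided, z = 1.960: Φ(0.64) = 0.74.

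The gap of ten points is there before any imputation.

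**3. The statistic carries no direction.** With moderate or severe pain in 44/80 on HBOT and 32/40 on control, HBOT is better by 25 points: chi-square = 7.18, P = 0.007. With 64/80 and 22/40, HBOT is worse by 25 points: chi-square = 8.21, P = 0.004. Both satisfy P < 0.05.

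**4. With imputation.** Trials of 80:40 were simulated with outcomes missing at random within arm and 20 proper within-arm imputations. The chi-square statistics d were pooled by the D2 rule:

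D2 = [mean(d) − (21/19)·r]/(1 + r), with r = (1 + 1/20)·var(√d), referred to an F distribution with 1 numerator degree of freedom.

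The risk difference was pooled by Rubin's rules, with total variance = mean within-variance + (1 + 1/20)·between-variance. The signed D2 test halves P and requires the mean difference to favour HBOT. Results from 8,000 trials per scenario:

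| Missing | Power, D2 at P < 0.05, no sign | Power, signed D2, one-sided 0.05 | Power, Wald risk difference, one-sided | 95% interval coverage |
|---|---|---|---|---|
| 5% | 0.761 | 0.850 | 0.868 | 0.939 |
| 10% | 0.739 | 0.839 | 0.859 | 0.943 |
| 20% | 0.697 | 0.802 | 0.824 | 0.944 |
| 30% | 0.629 | 0.745 | 0.771 | 0.944 |

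With both arms at 80%:

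| Missing | D2 at P < 0.05, no sign | of which HBOT worse | Signed D2, one-sided | Wald risk difference, one-sided |
|---|---|---|---|---|
| 5% | 0.0518 | 0.0278 | 0.0495 | 0.0695 |
| 10% | 0.0534 | 0.0298 | 0.0490 | 0.0639 |
| 20% | 0.0488 | 0.0270 | 0.0488 | 0.0645 |
| 30% | 0.0516 | 0.0284 | 0.0489 | 0.0621 |

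Monte Carlo standard error is about √(0.05×0.95/8000) = 0.002 for the error rates and √(0.75×0.25/8000) = 0.005 for power.

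**5. Other signed statistics** (10,000 trials each).
- Rubin-pooled score difference (difference in proportions with its null variance), 10% missing: one-sided error 0.048, power 0.846.
- Rubin-pooled log odds ratio: error 0.042; power 0.832 at 10% missing and 0.786 at 20%.
- Two-sided at 10% missing, D2 has power 0.740 and the pooled log odds ratio 0.725, so using chi-square with imputation loses no power in itself.

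**The case against.** Much of the case on the other side is right.

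- **The one-sided test can be recovered.** A reader might infer that a chi-square test on imputed data rules out a directional test. It does not. In a 2×2 table chi-square has one degree of freedom and is the squared difference in proportions over its null variance. Attaching the sign and halving P, or pooling that difference directly, keeps the level near 5%.
- **Imputation does not cost the ten points.** A reader might put the power gap down to pairing chi-square with imputation. Steps 2 and 5 show that it is sidedness.
- **There is an estimate.** A reader might infer that the declared difference is never estimated, or that the result is 20 separate P values. Proportions will be presented, the mean difference over the imputed datasets is a valid point estimate, and multiple imputation implies pooling. What the named analyses do not supply is the pooled standard error and interval.
- **A pooling formula may sit elsewhere.** An article may leave it to the full protocol or SAP, which are not shown. Its absence is no finding, and it cannot be inferred that the choice would be made after seeing the data.

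It can also be said that the one-sided rule in Sample size considerations governs the whole trial. That is a fair reading, but Data analysis names an unsigned test and a bare P < 0.05, and does not say how the two are joined. What remains is a mismatch between choices the article does state, so a fuller plan that followed them literally would inherit it.

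**Conclusion.** The point holds in this limited form. The stated primary test does not match the stated one-sided comparison, and it yields no interval for the stated primary quantity. Read without a sign at P < 0.05, power is about 74-75% at 10% missing and about 70% at 20%. Signed and one-sided, it is about 83-85% and 79-80%. Under equal rates, about 2.8% of all trials would be declared significant with HBOT worse, a result the directional test excludes.

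These figures rest on the protocol's 55% and 80%, all 120 patients randomised, an assumed missing fraction, missingness unrelated to outcome within arm, and imputation from arm alone. At 30% missing even the signed test falls to about 75%, so the fix does not protect against heavy loss. Neither the design nor the sample size is called into question.

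**What to change.** Reword the primary analysis in Data analysis along these lines:

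1. The primary result is the risk difference for moderate or severe pain at 3 months between allocated arms, estimated in each imputed dataset (for example by standardisation from a logistic model), pooled by Rubin's rules and given with a confidence interval. Coverage of the 95% interval is about 94-95% in these settings.
2. The primary test is one-sided at 0.05 in favour of HBOT, taken from one named signed pooled statistic: the Rubin-pooled score difference, the signed pooled chi-square, or the pooled log odds ratio. It should not be a Wald test on the pooled risk difference, whose one-sided error is about 6-7%.
3. State that this one-sided 0.05 is the threshold for the primary outcome, and say which sidedness the general P < 0.05 has for the other outcomes. Note that a 95% interval may include zero when the one-sided test rejects.
4. Keep the ordinary chi-square test for the complete-case sensitivity analysis, and the odds ratios as secondary.

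The cost is analysis wording and a few lines of code. No new data and no change in sample size are needed, and the article reports recruitment as ongoing, so the change could be made before analysis.
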